### Clinical Centers

The study will be conducted in 2 clinical centers: Universitätsmedizin der Johannes Gutenberg-Universität Mainz (Mainz, Germany) and IRCCS Istituto Romagnolo per lo Studio dei Tumori “Dino Amadori” (IRST, Italy).

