### Recruitment and Enrollment

Figure 3 describes the flow of patients throughout the study. All patients will be treated and monitored for their disease according to the local clinical practice, and no changes in treatment or follow-up will be decided based on participation in this study. At IRST Italy, patients in follow-up at clinical sites for acute myeloid leukemia or colorectal cancer disease and those considered eligible by the study oncologists will be invited to participate in this research. The oncologist will inform patients of the aims and procedures of the study. At Mainz, patients are prescreened by the treating health care professional (HCP) for eligibility and are introduced to the study by the HCP during their regular clinic visits. If the patient is interested, the HCP will give the patient’s name and the time of the next clinic visit to the study coordinator or study nurse. At the patient’s next visit, the study coordinator will meet the patient and enroll the patient by following the enrollment procedures.

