All patients will be informed that the participation is voluntary and that they are allowed to interrupt their participation whenever they want and for any reason. This will not prejudice the patient’s subsequent care. Patients will also be informed about relevant data protection and privacy legislation. A written, signed, informed consent form from the patient must be obtained before study entry. After signing informed consent, patients will be registered into ONCORELIEF electronic data capture system. Only deidentified data will be collected, including the data collected by the app or wearable device. Each patient will be assigned a unique alphanumerical ID, and only clinical site staff will have access to patients’ personal data and reidentification key. The anticipated total number of recruited patients will be 30 acute myeloid leukemia and 60 colorectal cancer for the 2 study phases. Therefore, for the pilot phase, an additional 25 patients with acute myeloid leukemia and 55 patients with colorectal cancer will be enrolled in total across clinical sites. Mainz will attempt to recruit about two-third of the patients, that is, up to 20 patients with acute myeloid leukemia and up to 40 patients with colorectal cancer. IRST is expected to recruit 20 patients with colorectal cancer (1 site in Italy, IRST IRCCS) and 10 patients with acute myeloid leukemia. However, due to the COVID-19 health crisis, fewer patients are coming to the clinic and the number might have to be adjusted. Patients are enrolled for 3 months.

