#### Measurement of the QoL and Well-being Index

The QoL and well-being composite index has a hierarchical structure of three levels: (1) global, (2) domains, and (3) needs. The first level represents the total QoL and well-being score. The second level includes 3 different need domains (emotional distress, psychophysiological, and physical). For example, the “emotional distress” domain includes the needs “depression” and “anxiety.” See Table 2 that presents the grouping of needs into domains and the instruments to assess the needs for each type of cancer, acute myeloid leukemia and colorectal cancer.

**Table 2 table2:** Domains and key needs assessed for each type of cancer.

Domain	Acute myeloid leukemia needs	Colorectal cancer needs
Emotional distress	Depression Anxiety	Depression Anxiety
Psychophysiological	Sleep Fatigue Lack of sexual interest	Fatigue
Physical symptoms	Sore mouth Appetite loss	Colitis Appetite loss Peripheral neuropathy Hand-foot syndrome
Well-being	Well-being	Well-being

The different scores at each level will provide a set of metrics that will allow to identifying and monitoring QoL and well-being of patients with cancer. This multilevel approach will provide information about what domain or domains (eg, emotional distress) related with patient needs (eg, depression, anxiety) must be improved or to identify differences by gender, type of cancer, and country at the 3 levels. The global index results from averaging the scores of each domain, which are based on the scores obtained in each patient’s key needs. The QoL and well-being global score is converted on a 0-1000 scale and will allow a qualitative appreciation, which will range between 400 (very poor) and 900 or higher (very good). Clinical and psychosocial recommendations coming from the ONCORELIEF system are analyzed and decided by the health professional and are focused on specific needs rather than the overall score. However, it is expected that a positive change in specific unmet needs will be reflected positively on the QoL and well-being index global score. Below we describe a user scenario illustration based on a fictitious case (see Figure 4) as an example of how the ONCORELIEF digitally assisted workflow may hopefully work in a real-life setting.

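### The index is said to identify differences by country, but each country has only one centre, so the data can show only a Mainz-versus-IRST difference

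*Protocol article*

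**What the plan says.** The claim is in the protocol article under Measurement of the QoL and Well-being Index. The index has global, domain and need levels, and the approach is said to help "identify differences by gender, type of cancer, and country at the 3 levels".

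The design facts that bear on it are these.

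- Clinical Centers: "The study will be conducted in 2 clinical centers", one in Mainz, Germany, and one (IRST) in Italy.
- Recruitment and Enrollment, size: "The anticipated total number of recruited patients will be 30 acute myeloid leukemia and 60 colorectal cancer for the 2 study phases". Mainz is to recruit "up to 20 patients with acute myeloid leukemia and up to 40 patients with colorectal cancer". For Italy, "IRST is expected to recruit 20 patients with colorectal cancer (1 site in Italy, IRST IRCCS) and 10 patients with acute myeloid leukemia".
- Recruitment and Enrollment, route: at IRST, patients in follow-up and "those considered eligible by the study oncologists will be invited to participate in this research". "At Mainz, patients are prescreened by the treating health care professional (HCP) for eligibility"; names of interested patients then go to the study coordinator or nurse, and the coordinator enrols them at the next visit. Disease care follows local practice.
- Psychosocial Instruments: one selection criterion was that validated Italian and German versions exist.
- Table 2: the needs that make up some domains differ between acute myeloid leukemia (AML) and colorectal cancer (CRC).

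**The concern.** To attribute a difference to country, one needs some way of telling it apart from a difference between the particular hospitals sampled. That takes at least two centres in a country, or outside information on how much centres vary. This design has neither. A German-Italian gap in the index could reflect the country, the hospital, who was approached and how, local supportive care, or the language version of the questionnaires. The article's Limitations section does not mention this.

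What is at stake is interpretation. A gap between two hospitals could be published as a gap in quality of life between two countries.

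A related point concerns cancer type in the same sentence. A comparison at all three levels presumes that the scores mean the same thing in both cancers, and Table 2 shows that some do not.

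**Working it through.** **1. The plan's own figures.** From Recruitment and Enrollment:

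- AML: 20 (Mainz) + 10 (IRST) = 30
- CRC: 40 (Mainz) + 20 (IRST) = 60
- Total: 30 + 60 = 90; Mainz share 60/90 = 66.7%, matching the stated two-thirds
- After 5 prepilot patients per cancer: 30 − 5 = 25 AML and 60 − 5 = 55 CRC, as stated

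The recruitment figures are consistent.

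**2. Can country be separated from centre?** Let country = 1 for Italy and centre = 1 for IRST. The two indicators are equal for all 90 patients. A design matrix with intercept, country, centre and cancer type has 4 columns and rank 3. With a single location term it has 3 columns and rank 3. So one location contrast is estimable, and it is Mainz versus IRST. This needs no assumption about alpha, power or variance.

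**3. Would more patients help?** Take the total variance as 1 and let ρ be the share of it that lies between centres within a country. Read as an estimate of the country difference, the observed contrast has

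SE = √[2ρ + (1 − ρ)(1/60 + 1/30)], where 1/60 + 1/30 = 0.05.

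The article gives no ρ, so these values are assumed:

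| ρ | SE (in SD) | Limit √(2ρ) with unlimited patients |
|---|---|---|
| 0 | 0.224 | 0 |
| 0.01 | 0.264 | 0.141 |
| 0.02 | 0.298 | 0.200 |
| 0.05 | 0.384 | 0.316 |
| 0.10 | 0.495 | 0.447 |

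A patient-level 95% interval has half-width 1.96 × 0.224 = 0.44 SD. It is valid for Mainz versus IRST but too narrow for Germany versus Italy whenever ρ > 0. The part due to centres does not shrink as patients are added, and ρ itself cannot be estimated with one centre per country.

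**4. Is cancer type tied to centre too?** No. AML makes up 20/60 = 1/3 of the Mainz target and 10/30 = 1/3 of the IRST target, so the planned correlation is 0. Nothing in the design ties gender to centre.

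**5. Do the scores have the same content in both cancers?** From Table 2:

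| Domain | AML | CRC | Same content? |
|---|---|---|---|
| Emotional distress | depression, anxiety | depression, anxiety | yes |
| Psychophysiological | sleep, fatigue, lack of sexual interest | fatigue | no |
| Physical symptoms | sore mouth, appetite loss | colitis, appetite loss, neuropathy, hand-foot syndrome | no |
| Well-being | well-being | well-being | yes |

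Five needs are shared: depression, anxiety, fatigue, appetite loss and well-being. (The text of Psychosocial Instruments names four as common; Tables 1 and 2 show appetite loss as shared too.) The global score averages the domains, so it inherits the mismatch.

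**The case against.** The strongest reply is that this is one descriptive clause in a measurement section. It states no hypothesis, test or causal attribution, and the pilot's four key questions and design aim are about feasibility. A difference between the German and Italian patients can be computed and described. All of this stands, and it limits the point to wording and interpretation. It does not rescue the label: the only difference that can be described is between two hospitals.

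It can also be said that the recruitment routes are not far apart. Both rest on a clinician's judgement of eligibility, and participation is voluntary at both. That is fair; the clear contrast is procedural. The aliasing does not depend on it.

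A reader might infer more than the article supports:

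- *Many contrasts will be tested, with chance findings or low power.* The article states no test by country, cancer type or gender. The number of tests and any error control are matters for an analysis plan that is not shown.
- *Gender and cancer type are confounded with centre.* They are not, by design (step 4).
- *Group differences will drive recommendations.* The article has recommendations decided by the health professional on specific needs, and nothing links them to group contrasts.

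**Conclusion.** The point holds for country. With one centre in each, country is fully aliased with centre, and so with recruitment route, local care and, presumably, questionnaire language. The design supports a Mainz-versus-IRST description and nothing wider, at any number of patients from these two centres. This rests only on the stated number and location of centres; the ρ values in step 3 are assumed and merely illustrate the consequence. That language version follows centre is an inference from the instrument selection criterion.

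For cancer type the issue is comparability of content, not aliasing: the psychophysiological, physical and global scores are built from different needs in AML and CRC.

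Severity is minor. No feasibility question, recruitment target or stated decision depends on a country comparison, and it would be wrong to conclude that the pilot's aims are compromised.

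**What to change.** Delete country from the sentence and add text such as:

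> Scores will be described by centre (Mainz versus IRST) within cancer type, with 95% confidence intervals. Differences between centres will not be interpreted as differences between countries.

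If scores are also described by cancer type, either restrict this to the five shared needs (depression, anxiety, fatigue, appetite loss, well-being) and to domains with the same content (emotional distress, well-being), or state that the psychophysiological, physical and global scores have different content in AML and CRC.

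The cost is a few sentences and no new data. The study gives up a between-country claim that it could not support. The Results section reports that analysis had not begun in January 2023, so at that date the wording could still be settled before any results were seen.

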**Figure 4 figure4:**
[figure not shown]
Pauline case illustration.

#### User Scenario Illustration

Shortly after Pauline was diagnosed with stage 2 colorectal cancer, she had surgery followed by chemotherapy as adjuvant treatment. She accepted the opportunity to use the ONCORELIEF Guardian Angel app, although she didn’t particularly like the idea of entering much data into an app. Over time, the Guardian Angel app, having connected with her smart device, identified patterns, which had been correlated with the early onset of fatigue in patients like Pauline: she napped more than before and was less active. Additionally, her ONCORELIEF QoL and well-being global score had dropped from 700 to 500. Her HCP got notified of these patterns through the ONCORELIEF service and, after some consideration, sent a message to the patient. When Pauline got notified the next day, she read the accompanying text and realized from the color coding on her app that her QoL and well-being index score had dropped further, and upon further investigation, she read that it was 500 because of early fatigue and some mild depressive symptoms. It then occurred to her that this may have been the reason behind her low motivation and her reluctance to get up and go to work in the morning. She gave consent for her new information to be shared with her HCP and was provided with a few minutes’ worth of reading material, which made her feel somewhat better since she realized this is relatively common and not a huge cause of concern. Her HCP, after viewing the report on Pauline’s responses as well as her recent history via ONCORELIEF, gave a recommended intervention: gradual exercise increase and get support from psycho-oncology services. The HCP agreed and soon enough Pauline had the recommendation on her Guardian Angel app. She felt OK but not great—but then read that the exercise coach would motivate her based on her achievements but also that her exercises would be tailored to her unique needs and preferences. The accompanying content offered a variety of exercises: since she had not had an ostomy surgery and did not have a stoma bag, she could also swim in the local pool, and she liked that idea. Pauline started tracking her swimming sessions simply with a couple of taps at a time. The psycho-oncologist assessed Pauline’s depressive cognitions and beliefs and her lack of motivation and pleasure in doing daily activities and suggested some stress management skills to cope with depression. After a few weeks, both Pauline and her HCP could see her ONCORELIEF Index QoL and well-being score increasing slowly but steadily to 700.

### Ethics Approval

The protocol, informed consent, and any accompanying material provided to the patient were submitted to the ethical board of IRST (CEROM, Comitato Etico della Romagna, case number Prot. 8528/2021) and Mainz (Ethik-Kommission der Landesärztekammer Rheinland-Pfalz, case 2021-16122) for review. The pilot study was approved by both ethical boards. Any modifications made to the protocol, informed consent, or material provided to the patient after receipt of the Ethics Committee approval must also be submitted by the investigator to the committee in accordance with local procedures and regulatory requirements. It is the responsibility of the investigator to obtain written informed consent from each subject prior to entering the trial or, where relevant, prior to evaluating the subject’s suitability for the study.

The investigators will ensure that this study is conducted in full conformity with the current revision of the Declaration of Helsinki (last amended 64th WMA General Assembly, Fortaleza, Brazil, October 2013), with relevant regulations and with the ICH Guidelines for Good Clinical Practice E6 (R2), and other relevant local legislation.

## Results

The ONCORELIEF project started in January 2020 and will end in June 2023. The pilot study started on September 1, 2022. As of January 2023, we enrolled 33 patients with colorectal cancer and 7 patients with acute myeloid leukemia. As of January 2023, we have not yet started the data analysis. We expect to get all data in June 2023 and expect the results to be published in the second semester of 2023.

## Discussion

### Principal Findings

The main objective of ONCORELIEF is the development of a user-centered AI system to facilitate the input and integration of patient-related biopsychosocial data to improve posttreatment QoL, well-being, and health outcomes. We hope that this project will be feasible and will provide patients and health professionals with a valuable tool to improve the holistic rehabilitation of patients with cancer. There has been increasing use of eHealth tools in health care in general [5] and in patients with cancer in particular [4,27,28], but the main innovation of ONCORELIEF is that all data of patients with cancer will run on a digitally assisted workflow of posttreatment supportive patient care supported by an AI system. The core concept of the ONCORELIEF proposal is based on the collection of biopsychosocial patient data to provide patient-centered care and better support services to patients with cancer and survivors of cancer. ONCORELIEF will enable identifying, collecting, harmonizing, modeling, and eventually processing and analyzing data from diverse channels and domains, using Big Data and AI techniques to develop services and features that will be offered to all cancer stakeholders, with the aim to serve them with a continuous monitoring and assistance app, toward increasing the awareness of their QoL and well-being status. The overall output of ONCORELIEF has the potential to provide insights for HCPs and caregivers, as well as for patients, and to deliver recommendations toward more effective psychosocial support. Patients may be more motivated to improve their health and hasten their way back to normal, through the adoption of healthy lifestyles and stress management skills. The power of ONCORELIEF lies on a holistic model of health, capturing ongoing data from diverse sources (eg, patient-reported outcomes through a smartphone app, physiological signals from a wearable smart device, and demographic and medical data from health records) involving the biological, psychological, and social dimensions of the patient with the potential to offer the patient just-in-time recommendations to cope with the unmet needs and challenges of the cancer journey.

### Strengths

The strengths of the study are as follows: the platform and patient-assessment profile are continuously updated and is available 24/7, the study has the potential of less demand of medical consultations since ONCORELIEF gives support to the patient all the time, and the study contributes to better clinical outcomes.

### Limitations

The limitations of this study are resistance from some patients who are not familiar with digital devices, eHealth tools and procedures are not yet integrated into hospitals’ data evaluation and recording systems, and platforms and systems such as ONCORELIEF may emerge as extra tools that can be felt as complications in the day-to-day life of HCPs.

## Appendix

Multimedia Appendix 1 Project Evaluation (Peer-Review by European Commission).

## Abbreviations

AI: artificial intelligence
HCP: health care professional
IRST: Istituto Romagnolo per lo Studio dei Tumori “Dino Amadori”
QoL: quality of life
